**Methods:**

XILO-FIST is a multicentre randomised double-blind, placebo-controlled, parallel group clinical trial funded by the British Heart Foundation and the Stroke Association. The trial has been adopted by the Scottish Stroke Research Network and the UK Clinical Research Network. The trial is registered in clinicaltrials.gov (registration number NCT02122718). XILO-FIST will randomise 464 participants, aged greater than 50 years, with ischaemic stroke within the past month, on a 1:1 basis, to two years treatment with allopurinol 300 mg twice daily or placebo. Participants will undergo brain magnetic resonance imaging, cognitive assessment, ambulatory blood pressure monitoring and blood sampling at baseline and after two years treatment. The primary outcome will be white matter hyperintensity progression, measured using the Rotterdam progression scale. Secondary outcomes will include change in white matter hyperintensity volume, mean day-time systolic blood pressure and measures of cognitive function. Up to 100 will undergo additional cardiac magnetic resonance imaging in a sub-study of left ventricular mass.

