### Randomisation

Participants are randomised (1:1) to receive either allopurinol or placebo orally for 104 weeks. Randomisation codes are stored securely on the Robertson Centre for Biostatistics (RCB, University of Glasgow) network, with restricted access. Eighty per cent of participants are allocated to treatments by a minimisation algorithm which includes presence of WMH at baseline and sub-study eligibility as minimisation factors, Randomisation carried out via the study web portal. A telephone interactive voice response system is available as a backup.

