### Assessment of WMH

The STRIVE recommendations are followed during image review.^16^ WMH of presumed vascular origin are defined as hyperintense lesions on T2-FLAIR and can appear as isointense or hypointense (although often not as hypointense as CSF) on T1-weighted sequences. All scans are reviewed blinded to treatment allocation.

A Fazekas and Scheltens scales is assigned.^17,18^ The Rotterdam progression score (RPS) and Schmidt’s progression score are calculated by simultaneous review of the baseline and two-year scans.^19,20^ All visual rating scales are assessed independently by two trained observers. Where there is any level of disagreement on a score, that score will be reviewed by at least two raters and a consensus score applied.

Volumetric assessment of WMH volume will also be performed. The first step in automated extraction of WMH volumes is to estimate the white matter area in each subject using atlas-based segmentation.^21^ A probability map of white matter created from 313 volunteers aged 18–96 years is used,^22^ and this map is registered to each subject using non-linear (diffeomorphic) registration to provide an initial estimate of white matter in each subject.^21^ Hyperintense outliers are identified on T2 FLAIR by transforming each voxel to a standard (z) score. Voxels with z ≥ 1.5 and within the estimated white matter area are initially defined as WMH. Final WMH estimates are defined by 3D Gaussian smoothing to reduce noise and account for partial volumes around WMH edges. Automatic WMH estimates are visually checked and infarcts masked by a trained image analyst following STRIVE guidelines.^16^ Normal-appearing tissues including cortical grey matter, sub cortical grey matter, cerebral white matter and supratentorial cerebrospinal fluid are segmented using population-specific tissue probability maps, within-patient T1 intensity data, and adjoining voxel data.^23,24^ Normal-appearing tissue segmentations are checked and edited in the same manner as WMH.

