### Statistical analysis

Full details of all statistical issues and planned statistical analyses will be specified in a separate statistical analysis plan which will be agreed before database lock and unblinding of treatment codes to the study statisticians.

All data will be summarised overall and by treatment group. Efficacy analyses will be carried out according to the intention-to-treat (ITT) principle, that is, in relation to randomised treatment allocation, regardless of treatments actually received. The population for ITT analyses will be all validly randomised participants, who do not have any major protocol violations. Additional analyses will be carried out using a per-protocol (PP) population, consisting of those members of the ITT population who remain on treatment as randomised and do not have any minor protocol violations. All protocol violations will be assessed and classified as major or minor, prior to database lock.

Unadjusted between-group comparisons of continuous and ordinal outcomes will be made using t-tests or Wilcoxon-Mann-Whitney tests as appropriate; categorical outcomes will be compared using Fisher’s exact tests. Adjusted analyses will use regression models, adjusted for variables used in the minimisation algorithm. Distributional assumptions will be assessed visually and where necessary, outcomes will be transformed, or a generalised linear model will be used with appropriate link and variance function. The model to be used for each outcome will be decided and documented prior to database lock. Treatment effect estimates will be reported with 95% confidence intervals and p-values.

Analysis of primary outcome – WMH progression is not expected to follow a normal distribution. Unadjusted comparison of treatment groups will use a Wilcoxon-Mann-Whitney test. A generalised linear regression model, with appropriate link and variance function, will be used to model WMH progression in relation to treatment and variables used in the minimisation algorithm. A further model will be fitted adjusting for other baseline characteristics found to be associated with WMH progression during blinded analyses, prior to database lock.

This model will be extended to assess the mediating effects of other study outcomes, such as changes in BP and UA post-randomisation.

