Analysis of secondary outcomes – secondary efficacy outcomes will be analysed using appropriate two-sample tests followed by regression analyses to estimate between-group differences adjusted for variables used in the minimisation algorithm. For outcome measures recorded at baseline as well as at follow-up, regression models will be adjusted for the baseline value. For endpoints measured at several time points, each time point will first be analysed separately, and then a repeated measures model will be applied to model measurements at all time points simultaneously.

Planned subgroup analyses – the moderating effects of baseline UA level in the primary analysis will be assessed through use of interaction terms in the model. These methods will also be used to investigate the moderating effects of other baseline characteristics in an exploratory manner.

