### Sample size

We assumed that 90% of participants would have evidence of WMH at baseline and that, over two years, approximately 64% would progress by one point or more on the RPS and that the mean progression score in the placebo group will be 1.293. This and the progression rate seen with a 30% reduction in WMH progression score are shown in Table 3. Based on a Wilcoxon-Mann-Whitney test, a sample size of 192 participants per group would give 80% power to detect this difference at a 5% significance level (nQuery Advisor® v7.0). This treatment effect is substantially less than the 80% relative reduction seen in the PROGRESS MRI study.^17^

Although we will minimise loss to clinical follow-up (completed for all except one participant in our pilot study), we have increased sample size to account for a 10% drop out rate seen in our pilot study and by an additional small amount to account for the fact that those with no WMH at baseline may progress at a lower rate. We will thus randomise 232 participants per group (10% drop outs will give data on 209 participants giving a further 17 participants (8%) per group to ensure sufficient power).

Other sample size calculations were based on two-sample t-tests. For ABPM, 101 participants per group will be required to give 80% power at a 5% significance level to verify the 3.3 mmHg reduction in systolic BP (SBP) seen in the recent meta-analysis^18^ (assumed SD of change in SBP 8.3). For the cardiac sub study, 25 participants per group would give 80% power to detect a 3.7 g difference in LV mass (assumed standard deviation 4.6). A 3.86 g difference was seen in a recent trial of allopurinol use in patients with type 2 diabetes.

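### The only baseline WMH term guaranteed in the adjusted primary model is presence or absence, which 90% are assumed to share; naming a severity measure would gain some precision at almost no cost

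*Protocol article*

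**What the plan says.** The Statistical analysis section of the protocol article gives the primary outcome three between-group analyses:

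- an unadjusted Wilcoxon-Mann-Whitney test;
- a generalised linear model that "will be used to model WMH progression in relation to treatment and variables used in the minimisation algorithm";
- a further model "adjusting for other baseline characteristics found to be associated with WMH progression during blinded analyses, prior to database lock".

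The Randomisation section describes a "minimisation algorithm which includes presence of WMH at baseline and sub-study eligibility as minimisation factors". The Sample size section states: "We assumed that 90% of participants would have evidence of WMH at baseline".

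The Run-in phase section makes a completed brain MRI a condition of randomisation. The Assessment of WMH section describes the Fazekas and Scheltens visual scales and adds: "Volumetric assessment of WMH volume will also be performed".

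For secondary outcomes the rule is: "For outcome measures recorded at baseline as well as at follow-up, regression models will be adjusted for the baseline value".

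**The concern.** The RPS is scored by viewing the baseline and two-year scans together, so it has no baseline value of its own. The baseline-adjustment rule for secondary outcomes therefore does not reach it. Two-year WMH volume, Fazekas score and Scheltens score, all secondary outcomes in Table 4, fall under that rule wherever a baseline value is recorded. The primary WMH outcome thus gets weaker baseline adjustment than the secondary WMH outcomes taken from the same scans.

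The plan itself treats baseline WMH as possibly prognostic: the Sample size section adds participants partly because those without WMH may progress more slowly. Yet the guaranteed covariate keeps only the crudest form of that information. It does not distinguish mild from severe disease among the 90% who have WMH, and minimisation does not balance severity within that group either.

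At stake is some power and a narrower confidence interval on the primary outcome, from data the trial already has. The covariates of the further model are also less firmly pre-specified than they could be, because they depend on their observed association with the outcome.

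**Working it through.** **Inputs from the article (Sample size):** 192 per group for 80% power at 5% (two-sided assumed), Wilcoxon-Mann-Whitney test; 232 randomised per group; 10% dropout; placebo mean RPS 1.293; 64% progressing by one point or more; 90% with WMH at baseline.

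**Assumptions, not in the article:** R², the share of RPS variance explained by baseline severity, taken as 0.05 to 0.30; an RPS standard deviation of about 1.42, from a negative binomial distribution on 0 to 9 matched to mean 1.293 and 36% scoring zero.

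**1. The plan's own figures.** 232 × 0.9 = 208.8, or 209 with data. 209 − 192 = 17, and 17/209 = 8.1%. Both agree with the article. The 192 cannot be reproduced: it needs the score distribution in each arm, and the table cited for it (Table 3) holds MRI sequence parameters. Assumed distributions give about 125 to 224 per group with tie correction, which brackets 192. It is taken as given.

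**2. How much the indicator can explain.** With a 90/10 split and a gap Δ in mean RPS between those with and without WMH, R² = 0.9 × 0.1 × Δ² / SD².

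- Those without WMH never progress: Δ = 1.293/0.9 = 1.437, so R² = 0.09 × 1.437² / 1.4187² = 9.2%.
- They progress at half the rate: the mean with WMH is 1.293/0.95 = 1.361 and Δ = 0.681, so R² = 2.1%.
- At 25% and 75% of the rate, R² is 4.9% and 0.5%.

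**3. Share of severity information kept by the indicator.** If presence of WMH is a cut at the lowest 10% of a normally distributed severity score, the share of linear information kept is φ(z)²/[p(1−p)] with p = 0.9, which is 0.342.

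**4. Power at 209 per group.** Power = Φ[(1.960 + 0.842) × √(209/192) / √(1−R²) − 1.960]. With R² = 0 this is Φ(2.923 − 1.960) = 83.2%. For the indicator, R² is replaced by 0.342 × R².

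| Assumed R² of severity | Power with indicator | Power with severity | Gain (points) | n per group equivalent to 192: indicator | n per group equivalent to 192: severity |
|---|---|---|---|---|---|
| 0.05 | 83.9% | 85.1% | 1.2 | 189 | 183 |
| 0.10 | 84.5% | 86.9% | 2.4 | 186 | 173 |
| 0.20 | 85.7% | 90.5% | 4.8 | 179 | 154 |
| 0.30 | 87.0% | 93.7% | 6.7 | 173 | 135 |

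The last two columns are 192 × (1 − 0.342 × R²) and 192 × (1 − R²), rounded up. In the bottom row the indicator is credited with 0.342 × 0.30 = 10.3%, slightly above the 9.2% ceiling in step 2, so that gain is if anything a little low.

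**Limits.** The factor 1 − R² belongs to a linear model. The RPS is skewed and ordinal, and a model with a non-linear link will not follow it exactly. The table gives an order of magnitude.

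**The case against.** The strongest reply is that the article leaves full analytic detail to a statistical analysis plan agreed before lock, and says the model for each outcome will be documented by then. That plan may name a severity covariate; it is not shown here. This stands as a caution. But the article does more than stay silent: it fixes the covariates of the adjusted model and fixes the route by which others enter. A plan that followed this wording would guarantee severity in none of the three analyses.

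Three stronger readings are tempting, and the article does not support them.

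- *A reader might infer that the plan ignores severity.* It does not. The further model admits "other baseline characteristics found to be associated with WMH progression during blinded analyses", which can include Fazekas, Scheltens or volume. Severity is not guaranteed, but it is not excluded. Nor is WMH presence the only covariate, since sub-study eligibility is also named.
- *A reader might infer that choosing covariates by outcome association biases the result.* The search is blinded to allocation, precedes database lock and affects only the further model. It cannot be steered towards an arm. The weakness is one of pre-specification.
- *A reader might infer that omitting severity makes the primary result unreliable.* Under randomisation the omission costs precision. The type I error rate already allows for chance imbalance, and the test used for sizing is unadjusted.

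It is also fair to say that the gain depends on an unknown R² and shrinks towards zero below 0.05, that the indicator is the right comparator because it is already in the model, and that 83.2% already exceeds the 80% target on the design assumptions.

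**Conclusion.** The point holds as a matter of efficiency and clear pre-specification. The only WMH term guaranteed in the adjusted primary model carries little information: at most about 9% of RPS variance, and about 2% if those without WMH progress at half the rate, given an SD near 1.42. A finer measure is available from a scan that every randomised participant must have.

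Naming it would gain about 1 to 7 power points over the indicator at 209 per group. That range rests on an assumed R² of 0.05 to 0.30, a normally distributed severity score cut at its lowest 10%, the linear-model approximation, and acceptance of the plan's 192. Validity is not in question. The change is worth making because it costs almost nothing and brings the primary outcome into line with the baseline adjustment planned for the secondary WMH outcomes.

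**What to change.** Before unblinding, state in the statistical analysis plan that the adjusted model for the RPS contains treatment, the minimisation factors and one named baseline WMH severity measure, for example Scheltens total or log WMH volume. Keep the unadjusted Wilcoxon-Mann-Whitney test, since the sample size rests on it. Label the model with data-selected covariates a sensitivity analysis.

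Nothing here requires a change of model family, the addition of age, or a lower standing for the Wilcoxon test; those are separate preferences.

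The cost is a sentence or two of wording and no new scans. If volume is chosen, the few participants whose baseline volume is unusable need a stated rule: use the visual score or a simple imputation. Choosing a visual score as the covariate would largely avoid this.

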### Sample size

We assumed that 90% of participants would have evidence of WMH at baseline and that, over two years, approximately 64% would progress by one point or more on the RPS and that the mean progression score in the placebo group will be 1.293. This and the progression rate seen with a 30% reduction in WMH progression score are shown in Table 3. Based on a Wilcoxon-Mann-Whitney test, a sample size of 192 participants per group would give 80% power to detect this difference at a 5% significance level (nQuery Advisor® v7.0). This treatment effect is substantially less than the 80% relative reduction seen in the PROGRESS MRI study.^17^

Although we will minimise loss to clinical follow-up (completed for all except one participant in our pilot study), we have increased sample size to account for a 10% drop out rate seen in our pilot study and by an additional small amount to account for the fact that those with no WMH at baseline may progress at a lower rate. We will thus randomise 232 participants per group (10% drop outs will give data on 209 participants giving a further 17 participants (8%) per group to ensure sufficient power).

Other sample size calculations were based on two-sample t-tests. For ABPM, 101 participants per group will be required to give 80% power at a 5% significance level to verify the 3.3 mmHg reduction in systolic BP (SBP) seen in the recent meta-analysis^18^ (assumed SD of change in SBP 8.3). For the cardiac sub study, 25 participants per group would give 80% power to detect a 3.7 g difference in LV mass (assumed standard deviation 4.6). A 3.86 g difference was seen in a recent trial of allopurinol use in patients with type 2 diabetes.

### Trial and data management

All study data will be held in the study Robertson Centre for Biostatistics, University of Glasgow, part of the UKCRC-registered Glasgow Clinical Trial Unit (number 16). A secure and restricted electronic data capture system (electronic case report form) will be used.

A Trial Management Group (TMG) meets regularly during the study.

#### Trial steering and data monitoring committees

A Trial Steering Committee meets at least annually and comprises an independent chair, three other independent members, a participant and/or a carer representative, the chief investigator and statistician. An independent data monitoring committee (IDMC) meets at least annually. This comprises of four independent members. Only the IDMC has access to unblinded outcome data before the trial ends.

### Summary and conclusion

XILO-FIST is designed to test whether allopurinol reduces the rate of WMH progression and BP in participants with recent ischaemic stroke. The hypothesis underlying XILO-FIST is that UA reduction and xanthine oxidase inhibition will improve vascular health and lower BP leading to a reduction in progression of WMH progression on MRI. If WMH progression is reduced, allopurinol could be an effective preventative treatment for people with ischaemic stroke and clinical endpoint studies would be needed. If allopurinol reduces BP after stroke, then it could be used to help people reach BP targets.
